## Abstract

**Background:**

Diminished ovarian reserve (DOR) is a condition that severely impacts female fertility, and there are currently no effective treatment strategies for DOR. Moxibustion may offer a non-invasive, low-risk intervention. This study aims to assess the clinical efficacy of moxibustion in improving ovarian reserve in women with DOR and to explore its underlying central neural mechanisms using resting-state functional magnetic resonance imaging.

**Methods:**

This prospective, single-center, parallel-group randomized controlled trial will be conducted at the Hubei Provincial Hospital of Traditional Chinese Medicine. Participants diagnosed with DOR will be randomly assigned in a 1:1 ratio to either an intervention group or a control group. They will both receive a lifestyle intervention. In addition, the intervention group will receive 16-week Yin-Yang Regulating Moxibustion. The primary outcome include changes in antral follicle count. Secondary outcomes include serum levels of anti-Müllerian hormone, follicle-stimulating hormone, and luteinizing hormonechanges in menopausal symptoms, anxiety, depression, and quality of life. Rs-fMRI will be used to investigate the brain’s central neural mechanisms.

**Discussion:**

The results of this study will provide new insights into the adjunctive treatment of DOR and elucidate its potential mechanisms through neuroimaging.

**Clinical trial registration:**

https://itmctr.ccebtcm.org.cn/, identifier ITMCTR2025001808

## Introduction

1

Diminished ovarian reserve (DOR) is a condition in women of reproductive age characterized by a reduced response to ovarian stimulation (1). It is typically identified by decreased anti-Müllerian hormone (AMH), reduced antral follicle count (AFC), and elevated basal follicle-stimulating hormone (FSH) levels (2).

DOR affects approximately 10% of women, often due to genetic, environmental, or lifestyle factors, and its prevalence exceeds 50% in women over 40 (3). As a major risk factors for female infertility, DOR accounts for approximately 10% of all cases of female infertility (4). In addition to impairing reproductive potential, DOR is associated with increased psychological burden, and diminished quality of life. Without timely intervention, DOR may progress to premature ovarian insufficiency (POI) or premature ovarian failure (POF), posing a serious threat to women’s reproductive health (2, 5).

Current therapeutic strategies for DOR remain limited and lack universally accepted clinical guidelines. Assisted reproductive technology (ART) is commonly employed to address infertility associated with DOR. However, ART procedures are costly and may impose a significant financial burden on patients. Moreover, due to the reduced quantity and compromised quality of oocytes in DOR patients, ART is often associated with lower fertilization rates and diminished pregnancy outcomes. More concerningly, accumulating evidence suggests that offspring conceived via ART may be at increased risk for adverse outcomes, including small-for-gestational-age birth, low birth weight, preterm birth, and congenital heart defects (6). Pharmacological interventions (e.g., coenzyme Q10, DHEA, GH, and sex hormones) aim to improve ovarian response and embryo quality, but their effectiveness remains debated and may be restricted by side effects or contraindications, including potential cancer risks (7–9). Therefore, there is an urgent need to develop safe, effective, and low-risk non-pharmacological interventions for the clinical management of DOR.

Moxibustion, a traditional Chinese medicine (TCM) therapy, refers to the ignition of moxa at acupoints or in specific areas. Through warmth and near-infrared stimulation, the active components of moxa penetrate the skin, stimulate meridians, and exert therapeutic and preventive effects on a variety of conditions (10). Compared to general moxibustion therapies, ginger-partitioned moxibustion (GPM), which combines the thermal effects of moxibustion with the pharmacological properties of ginger, may exert enhanced efficacy. Ginger is widely used in TCM and has been reported to possess antioxidant and free radical scavenging activities. Under the thermal stimulation of burning moxa, its bioactive constituents may be absorbed transdermally, enhancing the overall therapeutic effect in combination with moxibustion (11). In the present study, we adopted Yin-Yang Regulating Moxibustion (YYRM), a form of GPM that applies a compressed moxa discover a ginger medium placed on selected acupoints, including Mingmen (GV4) and Shenque (CV8).

Clinical studies have suggested that moxibustion may help regulate menstrual cycles, restore hormonal balance, improve ovarian blood flow, and increase pregnancy rates in women with ovarian dysfunction (12). However, most of the evidence has been limited to hormonal changes, improvements in clinical symptoms. Beyond these limitations, a recent study indicated that moxibustion may enhance the antioxidative defense system and inhibit apoptosis in naturally aging ovaries (13). While this provides additional biological evidence, such findings remain focused on peripheral ovarian effects and do not elucidate the central mechanisms by which moxibustion may exert its therapeutic actions. Currently, the mechanism by which moxibustion affects ovarian function is believed to involve regulating the hypothalamic–pituitary-ovarian (HPO) axis, leading to an improved ovarian microenvironment (12, 14). However, most of these research conclusions are derived from animal models.

From a neuroendocrine perspective, ovarian function is regulated through coordinated interactions between the central nervous system and peripheral endocrine organs, commonly conceptualized within the HPO axis. Previous studies suggest that DOR is not only a consequence of peripheral ovarian impairment, but may also involve altered central neuroendocrine regulation (15, 16). Dysregulation of hypothalamus-centered neural networks may influence gonadotropin secretion patterns and ovarian responsiveness, thereby contributing to ovarian reserve decline and providing a rationale for exploring central regulatory pathways using functional magnetic resonance imaging (fMRI).

fMRI, as a neuroimaging method based on blood-oxygen-level-dependent (BOLD) signals, reflects functional connectivity between different brain regions by monitoring changes in blood oxygen concentration in active brain areas (17). With unique advantages such as no radiation, non-invasiveness, high-quality imaging, and high spatial resolution, it has become one of the most widely applied tools for exploring brain function. Resting-state fMRI (rs-fMRI), one of the main types of fMRI, refers to the spontaneous neuronal activity in brain regions captured during the subject’s wakeful but resting state without specific cognitive tasks (18). Compared to task-based fMRI, rs-fMRI provides a better understanding of the brain intrinsic and spontaneous neural activity.

Direct DOR-specific neuroimaging evidence regarding hypothalamus-centered functional connectivity remains limited. Available DOR-related neuroimaging studies have begun to use rs-fMRI to investigate central functional alterations in patients with diminished ovarian reserve, and hypothalamus-centered functional connectivity frameworks have also been proposed in acupuncture-related DOR research (15, 19). These studies provide preliminary methodological support for applying rs-fMRI in this field, although direct evidence regarding hypothalamus-centered functional connectivity abnormalities in DOR remains insufficient. Evidence from POI studies may also provide indirect background information for ovarian dysfunction research (20). However, POI and DOR are distinct clinical entities with different degrees of ovarian dysfunction, and POI-related findings should not be directly extrapolated to DOR. In the present study, the hypothalamus was selected as a predefined seed region primarily because of its central role in reproductive neuroendocrine regulation within the HPO axis. Therefore, in the present study, the hypothalamus-centered, hypothesis-driven seed-based rs-fMRI design should be interpreted as an exploratory approach to investigate potential central regulatory changes associated with YYRM and ovarian reserve, rather than as confirmation of an established DOR-specific central pathological model.

In the assessment of ovarian reserve, AMH and AFC are both established markers with complementary clinical value. Previous evidence has shown broadly comparable predictive performance between AMH and AFC in predicting ovarian response (1, 21, 22). In the present study, AFC was selected as the primary outcome because it directly reflects the recruitable follicle pool and has been adopted as a primary endpoint in previous acupuncture-related DOR trials (23). In addition, FSH and LH were included as secondary endocrine outcomes because they are commonly used in the clinical evaluation of ovarian reserve and have been reported in previous studies of acupuncture interventions for DOR (24). Together, these indicators provide complementary information on ovarian reserve and reproductive endocrine status in this study.

This study aims to evaluate the clinical efficacy and feasibility of moxibustion combined with lifestyle intervention for DOR through a randomized controlled trial. In addition, rs-fMRI will be employed to explore the potential central neural changes associated with the therapeutic effects of moxibustion in DOR.

## Method

2

### Study design and setting

2.1

This prospective, single-center, parallel-group randomized controlled trial will be conducted at the Hubei Provincial Hospital of Traditional Chinese Medicine, including both outpatient and inpatient settings. The protocol follows the guidelines set forth in the Standard Protocol Items: Recommendations for Interventional Trials (SPIRIT) (25) for Interventional Trials (see Supplementary S1 File), and the results will comply with the Consolidated Standards of Reporting Trials (CONSORT) (26) standards for reporting trials. The study will span a total of 33 weeks, comprising a 1-week baseline period, a 16-week intervention phase, and a 16-week follow-up phase. The study flowchart and the schedule of assessments are presented in Figures 1, 2, respectively.

**Figure 1 fig1:**
[figure not shown]
Study schedule of enrolment, interventions, and assessments.

**Figure 2 fig2:**
[figure not shown]
Flowchart of the study.

### Ethical approval and consent to participate

2.2

The trial follows the principal ethical guidelines of the Helsinki Declaration and has received approval from the Ethics Committee of Hubei Provincial Hospital of Traditional Chinese Medicine (Ethic Approval NO. HBZY2025-C54-02). Written informed consent form will be obtained from all participants prior to enrollment. Our study has been registered in the International Traditional Medicine Clinical Trial Registry (ITMCTR2025001808, https://itmctr.ccebtcm.org.cn/). The results of the study will be published in a peer-reviewed academic journal.

### Trial status

2.3

This clinical trial is presently undergoing participant recruitment. The first participant was enrolled on May 19, 2025, following trial registration, with the enrollment period expected to be completed by December 2027. If participant recruitment is not completed within the planned timeframe, we will consider extending the recruitment period or increasing the number of centers as appropriate.

### Participants

2.4

#### Diagnostic criteria

2.4.1

According to the Bologna Conference standards of the European Association for Human-Assisted Reproduction, *the Guidelines Outlined in the Expert Consensus on the Clinical Diagnosis and Management of Diminished Ovarian Reserve 2022*, the diagnostic criteria for DOR include the following:Anti-Müllerian hormone (AMH) < 1.1 ng/mL;Antral follicle count (AFC) < 5–7 follicles in both ovaries during the early follicular phase (days 2–4 of the menstrual cycle)Basal follicle-stimulating hormone (FSH) ≥ 10 IU/L in two consecutive menstrual cycles.

#### Inclusion criteria

2.4.2

Female, aged 18 to 40 years, right-handed;Meets the diagnostic criteria for DOR;Able to undergo transvaginal ultrasound examination;Voluntarily participate in the research and sign an informed consent form.

#### Exclusion criteria

2.4.3

Participants meeting any of the following criteria will be excluded:History of polycystic ovary syndrome (PCOS), hyperprolactinemia, pituitary or hypothalamic amenorrhea, congenital reproductive tract malformations, or thyroid dysfunction as indicated by previous examinations;History of ovarian surgery, such as oophorectomy or ovarian tumor resection; history of chemotherapy or pelvic radiotherapy; history of immunosuppressant use;Combined with severe comorbidities affecting the cardiovascular, hematopoietic, neurological, or psychiatric systems, as well as diabetes mellitus, hypertension, etc.; hepatic dysfunction or renal dysfunction as indicated by previous examinations;Use of estrogen, progesterone, or dehydroepiandrosterone within 2 months before enrollment;Local skin damage or impaired thermosensation at the intervention site and any other condition that may render the participant unsuitable for acupuncture or moxibustion;Receipt of acupuncture or moxibustion intervention within the past 3 months;Evidence of organic brain lesions (e.g., cerebrovascular disease, epilepsy, or intracranial tumors) on MRI;Cognitive impairment;Participation in other clinical research trials within the past 6 months;Other reasons judged by the investigator that the patient is unlikely to comply with the protocol or is unsuitable for any reason (e.g., frequent prolonged business trips, etc.).

### Randomization, allocation and blinding

2.5

Randomization sequence will be generated using SPSS 24.0 and sealed in sequentially numbered, opaque envelopes. These envelopes will be delivered to an independent researcher responsible for outcome assessment. After obtaining written informed consent from eligible participants, the envelopes will be opened in sequence, and 66 participants diagnosed with DOR will be randomly allocated in a 1:1 ratio to either the intervention group (*n* = 33) or the control group (*n* = 33) based on the assignment enclosed to receive a 16-week intervention, respectively. Due to the particular nature of moxibustion research and practical clinical considerations, blinding of clinicians and participants is not feasible. To minimize potential biases, outcome assessments, data processing, and statistical analyses were conducted by independent third-party evaluators who were not involved in treatment implementation and were unaware of group assignments throughout the study period.

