This study innovatively integrates fMRI to investigate the impact of moxibustion on brain activity patterns. However, there are still several limitations in this trial: First, this study adopts an open-label design and does not include a sham moxibustion or placebo control. Due to the thermal and sensory characteristics of moxibustion, double-blinding of both participants and practitioners was not feasible, which may introduce expectancy bias. Therefore, the present study cannot fully separate the specific effects of YYRM from nonspecific effects associated with receiving active treatment. Second, our study is a single-center trial conducted solely in one hospital in China. thus, the findings require validation in larger, more diverse populations. Third, the sample size was relatively small, and this was a single-center, open-label study. These factors may limit the strength of the evidence generated by the present study. Therefore, the findings of this trial should be regarded as preliminary and interpreted with caution. Fourth, while the hypothalamus serves as a focused entry point for exploring ovarian-related central regulation, studies have also shown that other regions and networks may play a role in the central neuroendocrine regulation (48–50). We will consider investigating these regions in future studies, if necessary, to further elucidate the underlying mechanisms.

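### Section 2.5 contradicts itself: the allocation envelopes go to a researcher responsible for outcome assessment, yet outcome evaluators are said to be unaware of group throughout

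*Protocol article*

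**What the plan says.** Everything on allocation and blinding is in one paragraph of the protocol article, section 2.5 (Randomization, allocation and blinding). In order, it says:

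- The randomization list is produced in SPSS and "sealed in sequentially numbered, opaque envelopes".
- "These envelopes will be delivered to an independent researcher responsible for outcome assessment".
- After consent, "the envelopes will be opened in sequence" and 66 participants are allocated 1:1. The person who opens them is not identified.
- "blinding of clinicians and participants is not feasible".
- To limit bias, "outcome assessments, data processing, and statistical analyses were conducted by independent third-party evaluators", who took no part in treatment and "were unaware of group assignments throughout the study period".

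The limitations in section 3 (Discussion) confirm that the design is open-label without a sham, and say that "double-blinding of both participants and practitioners was not feasible, which may introduce expectancy bias". That remark concerns participants and practitioners. It does not mention outcome assessors and does not clarify who handles the envelopes.

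**The concern.** The only person the article connects with the allocation envelopes is someone whose stated job is outcome assessment. Whoever opens an envelope knows that participant's arm. An outcome assessor who opens envelopes is therefore not blinded, whatever the last sentence of the paragraph says.

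This matters more here than in many trials. Neither participants nor clinicians can be blinded and there is no sham, so the outcome assessor is the only party at the point of measurement who could be kept unaware of group. The primary outcome (section 2.7.1) is a transvaginal ultrasound count of follicles of 2–9 mm, where the operator decides which structures to count. HAMA and HAMD (section 2.7.2) are rating scales and depend on the rater. An observer who knows the arm can shift these results without intending to, and blinded data processing or analysis afterwards cannot undo a count that was biased when it was recorded.

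**Working it through.** No arithmetic applies. The question is whether the statements can be true together, so they are set side by side.

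| Step | What section 2.5 states | What it leaves open |
|---|---|---|
| Custody | Envelopes go to a researcher responsible for outcome assessment | Whether this person also scans or rates |
| Opening | Envelopes are opened in sequence after consent | Who opens them |
| Clinicians and participants | Not blinded | Nothing |
| Outcome assessment, data processing, analysis | Done by third-party evaluators unaware of group throughout | Whether the envelope recipient is one of these evaluators |

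**Step 1: does custody alone break the blinding?** No. The envelopes are sealed and opaque, so holding one reveals nothing. Opening it does.

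**Step 2: who opens?** The sentence on opening is in the passive and names nobody. It directly follows the sentence on delivery, and no other holder is mentioned. The natural reading is that the recipient opens the envelopes.

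**Step 3: is the recipient an outcome assessor?** The article describes the recipient by that function. The later sentence covers all outcome assessment and states that those who do it are unaware of group.

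**Step 4: combine.** If the recipient opens envelopes and assesses outcomes, the custody sentence and the blinding sentence are incompatible. They can be reconciled only by adding something the article does not say: that someone else opens the envelopes, or that the recipient only coordinates assessments and never scans or rates. No other section supplies either.

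**Step 5: which data are exposed?** Those an observer produces after allocation:

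- AFC at weeks 16 and 32. Section 2.8 bases the sample size on the AFC change from baseline to week 16, so the week 16 count is the one that matters most.
- HAMA and HAMD at weeks 16 and 32.

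AMH, FSH and LH are serum measurements and less open to an observer's knowledge of the arm. Data processing and statistical analysis have their own blinding claim, which envelope custody by an assessor does not by itself undo.

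**Step 6: is this still live?** Yes. Section 2.3 reports the first enrolment on May 19, 2025, with recruitment continuing and expected to finish by December 2027. The sentence describes a procedure in use.

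**The case against.** The strongest reply is that unblinding is inferred and not stated. The envelopes are sealed and opaque and the opener is unnamed. The article speaks of one independent researcher when describing custody and of several third-party evaluators when describing assessment, so the recipient might be a coordinator who never scans or rates. The paragraph plainly intends blinded assessment, and the custody sentence may be a drafting slip.

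Most of this stands as a limit on the conclusion. A reader might infer that assessor blinding is already lost; the text makes that likely but does not establish it. A reader might also infer that no blinding would remain; that is not so, because blinded data processing and analysis are claimed in the same paragraph and the hormone assays are less exposed. It is also tempting to express the harm as a shift in follicle count, but the article contains nothing on how far an unblinded reader would move the count, so any such figure would be invented.

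The reply does not remove the contradiction. Nor is this a detail an article may leave to a fuller protocol: the article positively assigns the envelopes to the wrong function. A fuller document might show what is really done, but it could not make these two sentences agree as they stand. Even a drafting slip needs correcting, because staff following the text would put allocation in an assessor's hands.

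**Conclusion.** The point holds as an internal contradiction in section 2.5. The envelopes are delivered to a researcher responsible for outcome assessment, with no other holder or opener named, while outcome evaluators are described as unaware of group throughout.

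The consequence is conditional. If the recipient opens the envelopes and also scans or rates, assessor blinding is defeated for the primary AFC comparison and for HAMA and HAMD, and the main protection against detection bias in an open-label trial without a sham is gone. If the recipient does not open them, or does not assess, the fault lies in the wording alone. The article does not settle which applies.

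No numerical size is given, because the document offers no basis for one. The conclusion rests on two readings: that the person who receives the envelopes also opens them, and that being responsible for outcome assessment includes making the assessments. Both are natural; neither is stated. The correction is needed in either case, since an assessment made by someone who knows the arm cannot later be made blind.

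**What to change.** 1. Establish who currently holds the envelopes, who opens them, and who performs the scans and ratings.
2. Assign holding and opening to an existing team member with no role in recruitment, outcome assessment, data processing or analysis.
3. State that nobody who has opened an envelope may perform post-randomization AFC scans or rate HAMA or HAMD.
4. Rewrite the custody sentence and the blinding sentence in section 2.5 so that they agree, and name by role who opens the envelopes.
5. If practice already separates these roles, correcting the sentence on who receives the envelopes is sufficient.
6. If an assessor has already opened envelopes, flag the affected week 16 and week 32 AFC, HAMA and HAMD assessments and add a sensitivity analysis for them. Apply the separation at once to remaining participants.

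The cost is reassigning one duty and a minor amendment. This assumes the team includes someone outside those four functions; the article does not list its staff. Sample size, outcomes and visit schedule are unchanged.
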